### Statistical methods

Data will be assessed for normality of distribution and transformed as appropriate. The active intervention (Cholecalciferol) and placebo groups will be compared at baseline to determine the effectiveness of randomisation. Euglycaemic clamp data from a healthy, non-uraemic cohort will be supplied by IH and used for comparison. Any differences between the groups that may cause potential confounding (age, sex, ethnicity, BMI, lean:fat mass, eGFR, calcium, phosphate, PTH, inflammatory markers, proteinuria) will be assessed and adjusted for in the analysis by the use of appropriate multivariate techniques.

Statistical analyses will be performed using standard statistical software (Stata Version 10.0, Texas, USA). For parametric continuous data, results will be expressed as mean ± standard deviation, for non-parametric continuous data, results will be expressed as median (interquartile range, IQR), and for categorical data, results will be expressed as frequencies (percentages %). The degree of association between 25-hydroxyvitamin D and the variables of interest will be assessed using Pearson's correlation for continuous normally distributed variables and Spearman's correlation for categorical or non-parametric data. Linear or binary logistic regression will be performed as appropriate and standard regression diagnostics will be performed. Comparison of means for independent samples will be made using: unpaired t-test (parametric data); Mann-Whitney test (non-parametric data); and, Fisher's exact test or Pearson's Chi-square test (categorical data). Comparisons of means for dependent samples will be by paired samples t-test (parametric data); Wilcoxon signed rank test (non-parametric data); and, McNemar's test (categorical data).

No interim analysis is planned, but patients will be monitored for safety by biochemical testing (serum calcium and phosphate) at 3 months. Analysis of insulin resistance related to intervention will be by completed cases only. Secondary hypotheses will be assessed by analysis of available data and intention to treat.

The hypothesis will be accepted if the null hypothesis can be rejected at the 0.05 probability level.

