### Sample size and randomisation

Prospective power calculations based on independent t testing indicate that the study will have adequate statistical power (80% probability) to detect a clinically significant increase in insulin sensitivity of 12%, assuming α = 0.05 and a population standard deviation of 10%, if 24 patients are recruited in the study (12 in each group). Using paired t testing for dependent sampling (non-randomised group, baseline to end of study), 8 patients will be needed. From previous experience within the renal unit of CKD trials, it is known that there is a high drop out rate because of progression to dialysis, death, intercurrent co-morbidity and loss to follow up. Allowing for a 20% drop out and using the adjustment factor 1/(1-*v*)^2^, a total of 51 patients will need to be recruited.

Randomisation will be by permuted block and stratified for baseline Body Mass Index (BMI, ≤25 Kg/m^2 ^and >25 Kg/m^2^) and diabetic status. Randomisation will be performed off-site using a validated Microsoft Access Computer based system available through the Centre for Clinical Research Excellence Vascular and Metabolic Health at the University of Queensland. This will generate a unique treatment allocation number which will be ascribed to the patient blindly by the physician. Pharmacy will be un-blinded and dispense trial medication based upon the numeric reference prescription, using unmarked bottles, with generic administration details.

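### In the randomised comparison, covariate adjustment is triggered by observed baseline imbalance instead of a short set fixed in advance; the rule is mildly conservative and gives up power

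*Protocol article*

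**What the plan says.** Under Statistical methods, the protocol article states that the cholecalciferol and placebo "groups will be compared at baseline to determine the effectiveness of randomisation". The next sentence brings in clamp data from a healthy, non-uraemic cohort for comparison. The one after it says that "Any differences between the groups that may cause potential confounding" will be assessed and adjusted for by suitable multivariate methods. Its list has 11 entries: three demographic (age, sex, ethnicity), two on body size and composition (BMI, lean-to-fat ratio), two renal (eGFR, proteinuria), three mineral (calcium, phosphate, PTH) and inflammatory markers, which are themselves a group.

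The section sets no threshold for a difference and fixes no covariate set. It lists the unpaired t-test and the Mann-Whitney test for independent samples, and linear regression where appropriate. The hypothesis is to be decided at the 0.05 level, but the section does not say whether an adjusted or an unadjusted result decides it.

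Under Outcomes, the primary measure is the change in glucose disposal rate, measured at baseline and end of study. Under Sample size and randomisation, allocation is stratified by BMI and diabetic status. Neither diabetic status nor baseline glucose disposal rate is among the 11 entries.

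**The concern.** If allocation was carried out properly, any baseline difference between the two randomised arms is a chance difference, and comparing the arms cannot show whether randomisation was effective. Nor does the size of an observed imbalance say whether a covariate is worth adjusting for. A strongly prognostic variable improves precision even when it is balanced. An imbalanced variable unrelated to outcome only costs precision, because it is correlated with treatment in that sample.

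The rule therefore makes the model depend on the data and tends to pick the covariates that are most collinear with treatment. It leaves out two candidates with a clear claim: the baseline value of the outcome and a stratification factor. The trial plans only 24 evaluable randomised patients at 80% power, so there is little precision to spare. The wording also leaves open which adjusted model, if any, decides the primary hypothesis.

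**Working it through.** **Inputs from the document (Sample size and randomisation).** Effect 12%, "a population standard deviation of 10"%, α = 0.05, power 80%, 12 per group, 8 for the paired group, 20% drop-out, inflation 1/(1−v)², total 51. Sidedness is not stated; two-sided reproduces the figures.

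**Assumed, because the document gives no value.** The threshold for calling a difference, the correlation among covariates, and the share of outcome variance that they explain (R²).

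**1. The plan's own figures.**
- Two-sample t-test, noncentrality (12/10)·√(n/2): 11 per arm gives 76.3% and 12 per arm gives 80.2%. So 12 per arm is right.
- Paired t-test, noncentrality (12/10)·√n: n = 7 gives 75.4% and n = 8 gives 82.8%. So 8 is right.
- Total: 24/0.64 = 37.5, rounded up to 38; 8/0.64 = 12.5, rounded up to 13; 38 + 13 = 51.
- Randomised patients analysed: 38 × 0.64 = 24.3 on the plan's own factor, or 38 × 0.80 = 30.4 at a plain 20% loss. So about 12 to 15 per arm.

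**2. Chance imbalance under perfect randomisation.** With 11 independent covariates and a p<0.05 screen: 1 − 0.95¹¹ = 0.431. With a p<0.20 screen: 1 − 0.80¹¹ = 0.914. At an assumed pairwise correlation of 0.3, simulation gives about 0.38 for the p<0.05 screen.

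**3. Power at the planned effect, 12 per arm (simulation, total outcome SD 10, p<0.05 screen).**

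| Covariates | Unadjusted t-test | Imbalance-selected model | Prespecified ANCOVA |
|---|---|---|---|
| Independent, none prognostic | 0.80 | 0.74 | 0.78 (one useless covariate) |
| Independent, one with R² 0.3 | 0.81 | 0.76 | 0.91 |
| Independent, one with R² 0.5 | 0.81 | 0.76 | 0.97 |
| Correlation 0.3, R² 0.4 overall | 0.80 | 0.79 | not run on a short set |

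A looser p<0.20 screen with independent covariates gives 0.66 to 0.73 for the selected model. At 15 per arm the p<0.05 screen gives 0.85 to 0.87, against 0.89 unadjusted and 0.96 to 0.99 for the prespecified ANCOVA (R² 0.3 to 0.5).

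**4. Type I error.** With no prognostic covariate, the selected model sits at about 0.05. With prognostic covariates (R² 0.3 to 0.5) it is about 0.04 to 0.045 under the p<0.05 screen and about 0.03 to 0.037 under the p<0.20 screen. Prespecified ANCOVA stays at 0.047 to 0.054, nominal within simulation error.

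**5. Price of a fixed three-covariate model.** At N = 24, residual degrees of freedom fall from 22 to 19. If none of the three were prognostic, the expected inflation of the treatment variance would be (N−3)/(N−3−k) = 21/18 = 1.17. Ignoring the small change in the critical value, the model breaks even when the three together explain 1 − 18/21 = 14% of outcome variance. The formula treats covariates as left to chance; stratified factors are closer to balance, so their cost should be lower.

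**The case against.** The strongest reply has five parts.

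- **No test is stated.** The text speaks of comparing and assessing and gives no threshold. This stands: the p<0.05 screen is an assumption. The only between-group methods listed are significance tests, however, and judging by eye would fix the model even less.
- **The groups in question may include others.** The sentence follows the mention of the healthy cohort, and the Intervention section allows an independent analysis of the non-randomised patients. Confounding is real in both comparisons, so a reader who concluded that all adjustment should go would be wrong. The randomised arms are still the groups named just before, and nothing exempts them. The completers-only primary analysis could also produce differences that are not pure chance, but choosing covariates by imbalance is not a planned remedy for drop-out.
- **The power loss can vanish.** With correlated prognostic covariates (R² 0.4 assumed), selected against unadjusted power was 0.79 v 0.80 at correlation 0.3 and 0.82 v 0.81 at 0.5. This stands: the loss against the planned t-test is at most about 6 points under a p<0.05 screen and may be nil.
- **Details belong to an analysis plan.** Threshold and model form may be settled there, and an unadjusted primary t-test is a possible reading, since the sample size rests on it. But tying adjustment to observed differences is a rule that the article itself states, and a plan that followed it would inherit the fault.
- **The omissions are defensible.** Analysing change already uses the baseline value in part, and stratification already balances diabetic status. Both are true, but neither replaces using these variables as covariates to gain precision.

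**Conclusion.** The point holds for the randomised comparison, at moderate size. Imbalance is the wrong trigger for adjustment, and the list omits baseline glucose disposal rate and diabetic status. Under an assumed p<0.05 screen at 12 per arm, power is about 0.74 to 0.79 against 0.80 planned, and type I error is at or somewhat below 5%. The larger cost is the forgone gain: about 0.91 with one prespecified covariate of R² 0.3. That R² is assumed; the document gives nothing from which to estimate it.

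Two stronger conclusions might be inferred and are not supported. The first is that power collapses to about 0.48. That requires all 11 entries in the model with none prognostic, whereas the plan adjusts only for those that differ, about 0.55 of them on average under the assumed screen (11 × 0.05). The second is that the false-positive rate rises to about 13%. That requires an analyst to report the smallest p-value across the unadjusted and single-covariate models. The plan leaves the deciding model open but describes no such search, and the rule applied as written is conservative.

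**What to change.** For the randomised comparison:

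- Present baseline data descriptively by arm, and remove the statement that the comparison shows whether randomisation was effective.
- Remove observed difference as the trigger for adjustment.
- Name one primary model in advance: change in glucose disposal rate on treatment, with baseline glucose disposal rate, BMI stratum and diabetic status as covariates. State that its treatment estimate decides the hypothesis at 0.05.
- Label any other adjustment as a sensitivity analysis that does not change the primary conclusion.

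For the comparisons with the non-randomised group and the healthy cohort, keep confounder adjustment, say that it applies there, and list the covariates beforehand.

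The cost is a change of wording and three residual degrees of freedom. No further data are needed, since baseline clamp, BMI and diabetic status are already collected. If the three covariates turned out not to be prognostic, the model would lose a little power compared with the plain t-test.

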### Outcomes

All outcome measures will be performed at baseline and end of study. The primary outcome measure will be a change in the glucose disposal rate as a marker of insulin sensitivity as measured by the hyperinsulinaemic euglycaemic clamp[58]. Secondary outcome measures will include serum PTH, cytokines (IL-1β, IL-6, TNFα), adiponectin (total and High Molecular Weight), osteocalcin (carboxylated and under-carboxylated), and peripheral blood mononuclear cell NFκB p65 binding activity, all of which will be tested on -80°C stored serum (nuclear extract for NFκB) in batch by enzyme-linked immunosorbent assay (ELISA). Brachial artery reactivity, aortic pulse wave velocity and waveform analysis, and indirect calorimetry will also be assessed.

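### Adjustment of the primary comparison depends on imbalances seen after randomisation, from a list without baseline glucose disposal rate or diabetic status

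*Protocol article*

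**What the plan says.** Under Outcomes, the protocol article states: "The primary outcome measure will be a change in the glucose disposal rate as a marker of insulin sensitivity", by clamp. It adds: "All outcome measures will be performed at baseline and end of study". A baseline clamp value is therefore planned for every patient.

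Under Sample size and randomisation: "Prospective power calculations based on independent t testing indicate that the study will have adequate statistical power (80% probability". The inputs are a 12% increase, an SD of 10%, α = 0.05 and 12 patients per group. The same section states: "Randomisation will be by permuted block and stratified for baseline Body Mass Index", and diabetic status is the second stratification factor.

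Under Statistical methods, the means of independent groups are compared as follows: "Comparison of means for independent samples will be made using: unpaired t-test (parametric data); Mann-Whitney test (non-parametric data". The same section has the arms compared at baseline to judge whether randomisation worked. Potentially confounding differences are then adjusted for by multivariate methods, from a list of 11 items: age, sex, ethnicity, BMI, lean:fat mass, eGFR, calcium, phosphate, PTH, inflammatory markers and proteinuria. Linear regression is mentioned for use where appropriate, without an outcome or covariates. The insulin resistance analysis uses completed cases.

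**The concern.** Read together, the sample size and statistical methods sections make an unpaired t-test on change the evident primary comparison, with adjustment decided after baseline differences have been seen. This rule is badly fixed in three respects.

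- The outcome's own baseline, probably its strongest predictor, is not on the list.
- Diabetic status is important enough to stratify on but is also not on the list.
- BMI is listed, but the trigger is an observed imbalance. Stratification is there to prevent imbalance in BMI, so the rule tends to leave it out.

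Three things are at stake. With 11 candidates and about 12 patients per arm, the covariates of the primary model are open to choice after the data are seen. A change score leaves regression to the mean in the estimate when the arms differ by chance at baseline. An analysis without the stratification factors also reports a standard error that does not reflect the precision the stratification has bought.

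**Working it through.** **Inputs from the article:** difference 12, SD 10, α 0.05 (taken as two-sided), 12 per group, 1:1 allocation.

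**Assumed, because the article does not give them:** the baseline-to-end correlation ρ, and the share R² of outcome variance explained by the strata. The article also does not say whether 10% is the SD of the change or of a single measurement. The main calculation takes it as the SD of the change.

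**1. The plan's own figure.** Noncentrality = (12/10)/√(2/12) = 2.94 on 22 df, which gives 80.2% power. With 11 per group it is 76.3%. The stated 12 per group reproduces.

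**2. Baseline as a covariate.** With equal variances at both times, the residual variance after adjusting for baseline is (1+ρ)/2 of the variance of the change. The adjusted SD is therefore 10·√((1+ρ)/2). The model has arm, baseline and two stratum terms, so 22 − 3 = 19 df. No credit is taken for variance explained by the strata. The cautious column also multiplies the variance by (2n−3)/(2n−6) = 21/18 for chance covariate imbalance.

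| ρ | Adjusted SD | Power, 3 df lost | Power, cautious | t-test on change |
|---|---|---|---|---|
| 0.3 | 8.06 | 93.3% | 89.3% | 80.2% |
| 0.5 | 8.66 | 89.6% | 84.6% | 80.2% |
| 0.7 | 9.22 | 85.6% | 80.0% | 80.2% |
| 0.9 | 9.75 | 81.6% | 75.5% | 80.2% |

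If 10% were instead the SD of a single measurement, the SD of change would be 10·√(2(1−ρ)) and the adjusted SD 10·√(1−ρ²). At ρ = 0.3 and 12 per arm, the t-test on change then has 66.1%, against 83.2% adjusted (77.2% cautious). At ρ = 0.7 the figures are 95.2% against 97.4% (95.1% cautious).

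**3. Regression to the mean.** With equal variances, a baseline difference D between arms shifts the expected difference in change by −(1−ρ)·D. Without regard to stratification, D has a standard deviation of √(2/12) = 0.41 baseline SDs at 12 per arm. At ρ = 0.5 an SD of change of 10 implies a baseline SD of 10/√(2·0.5) = 10. A one-standard-deviation imbalance (4.1) then moves the estimate by 0.5 × 4.1 ≈ 2.0, against a target difference of 12. Over repeated randomisations the average shift is zero.

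**4. Stratification factors.** Simulation with permuted blocks of 4 (assumed) in four strata, N = 24, 6,000 replicates per scenario:

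| R² | Type I error, unadjusted | Type I error, adjusted | Power, unadjusted | Power, adjusted |
|---|---|---|---|---|
| 0 | 5.2% | 5.0% | 80.7% | 79.8% |
| 0.1 | 4.2% | 5.2% | 80.6% | 83.0% |
| 0.2 | 3.2% | 4.9% | 82.0% | 87.2% |
| 0.4 | 1.8% | 5.1% | 84.4% | 94.9% |

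At R² = 0.4 the mean unadjusted standard error is 4.08, while the estimate's actual standard deviation is 3.34. The mismatch is on the conservative side.

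**The case against.** The strongest reply is that the quoted sentence is a general menu of tests by data type and does not name the primary outcome. The article is also condensed, and the exact covariates of a primary model are often left to a fuller document. This is fair as far as it goes. A missing covariate list alone would not be a finding. The article does more than stay silent, however. It sets a rule for when to adjust and lists what may be adjusted for, and that rule is what is at fault. The sample size section also points to the t-test as the primary comparison.

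A reader might infer that the plan ignores baseline glucose disposal rate and both stratification factors. The text does not support that. Baseline enters by subtraction, because the outcome is a change. BMI is on the conditional list, and multivariate adjustment is provided for. What is missing is baseline as a covariate, diabetic status altogether, and advance commitment to any of them.

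It also stands that the power gain is not unconditional. Under the cautious penalty it has gone by ρ = 0.7 and is a loss of about 5 points at ρ = 0.9. That penalty probably overstates the cost, since stratified blocks largely balance the strata, and it credits no variance explained by them.

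**Conclusion.** The concern holds as a matter of pre-specification and efficiency. Adjustment of the primary comparison is triggered by observed imbalance, and the candidate list leaves out the outcome's baseline and one of the two stratification factors.

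The power at stake at 12 per arm, if 10% is the SD of change, runs from about 13 points at ρ = 0.3 to about 1 point at ρ = 0.9. On the cautious calculation it runs from a gain of 9 points to a loss of about 5. Strata that explain 20% to 40% of the variance would add roughly 5 to 10 points. All of this rests on assumed ρ and R², so the size is uncertain even though the direction of the recommendation is not.

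Two stronger conclusions are tempting but unsupported. One is that the mismatch with stratified randomisation produces false positives: the unadjusted test is conservative, with simulated type I error of about 5% falling to about 2%. The other is that the sample size is wrong: 12 per group gives 80.2% power for the stated inputs. The change-score estimate is also unbiased over randomisation, so regression to the mean matters only given a chance imbalance in the trial as realised.

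**What to change.** Replace the imbalance-driven rule for the primary outcome with a model fixed in advance: linear regression of end-of-study glucose disposal rate on allocated arm, baseline glucose disposal rate, BMI stratum and diabetic status. The arm difference with its 95% CI is the primary result. State the condition for transforming the outcome in the same place. Keep the unpaired t-test or Mann-Whitney on change, and any adjustment prompted by baseline differences, as sensitivity analyses.

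The change is to wording only: the baseline clamp and both stratification factors are already collected. The price is 3 degrees of freedom (19 instead of 22 at 12 per arm), with little or no gain in power if ρ is high and the strata explain little. The sample size need not change.

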## Discussion

To date, no randomised controlled trial has been performed in pre-dialysis CKD patients to study the correlation between vitamin D status with supplementation, insulin resistance and markers of adverse cardiovascular risk. Given the limitations of active vitamin D compounds, we remain hopeful that cholecalciferol may be a safer intervention, with health benefits beyond those related to bone-mineral homeostasis. Ultimately, this trial will add much needed, controlled, prospective data to the field, and if positive, lead the way for a larger study focussed on addressing patient level outcomes in this challenging population.
